### 2.6. Serum Marker Evaluation

At timepoints T0 and T2, peripheral venous blood samples will also be collected to carry out a panel of blood chemistry tests to research biomarkers that may correlate with PSs and/or with the response/non-response to PNE. Specifically, based on the data in the literature, serum levels of CRP, ESR, IL-6, IL-8, TNF-α, and CGRP will be measured. CRP and ESR will be determined according to the standard method currently used at the IRCCS Humanitas Research Hospital clinical analysis laboratory. IL-6, IL-8, TNF-α, and CGRP will be assessed through an enzyme-linked immunosorbent assay (ELISA) following the manufacturer’s instructions, as reported elsewhere [17,39].

### 2.7. Statistical Analysis

#### 2.7.1. Sample Size

The population of the prospective group will consist of 30 consecutive early-stage TNBC patients recruited from our institution’s oncology department. Given the innovative nature of this study, which focuses exclusively on early-stage TNBC patients and utilizes PNE interventions administered by specialized staff, the sample size was determined based on prior prospective studies employing similar interventions [40].

To ensure the representativeness of our results and account for potential dropouts, we have incorporated a margin for sample attrition. Based on typical dropout rates observed in clinical studies, we anticipate a dropout rate of approximately 20%. Therefore, to achieve our target of 30 evaluable patients, we plan to initially recruit 36 patients (30/0.8), ensuring that the final sample size remains robust even if some participants withdraw from the study. This approach will help guarantee that our findings are statistically significant and reflective of the broader population of early-stage TNBC patients undergoing PNE interventions. 

Based on preliminary analyses regarding the study’s primary objective, we will evaluate whether the number of participants should be increased to 50 to identify any factors associated with a better or poor response to the study intervention.

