## Abstract

The treatment of early triple-negative breast cancer (eTNBC) has improved patients’ prognosis but often leads to adverse events and sequelae affecting quality of life (QoL). Pain Neuroscience Education (PNE) is a promising non-pharmacological intervention in this field. Preliminary data have shown the beneficial effect of PNE in BC survivors. However, there are still gaps in knowledge regarding its optimal use in eTNBC. To address this issue, a prospective pilot study will enroll 30 consecutive patients diagnosed with eTNBC at IRCCS Humanitas Research Hospital. The PNE program will consist of 10 weekly sessions to be started within 4 weeks of the onset or worsening of a pain syndrome (PS). QoL, pain, and disability will be assessed before, during, at the end of, and 6 months after PNE using validated questionnaires. Peripheral venous blood samples will be taken before and at the end of PNE to evaluate inflammatory serum biomarker levels. The primary objective is to evaluate whether PNE leads to clinical improvement in QoL and pain. If successful, it will be validated in a larger multi-centric cohort, potentially leading to its widespread implementation as a standard pain management tool for eTNBC patients.

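### Section 2.7.1 gives 36 as the result of 30/0.8, which is 37.5 (38 patients); the abstract's enrolment figure and the claim about significance also need correcting

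*Protocol article*

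**What the plan says.** Section 2.7.1 of the protocol article opens with the study size: "The population of the prospective group will consist of 30 consecutive early-stage TNBC patients". It gives the source of that number as precedent: "the sample size was determined based on prior prospective studies employing similar interventions".

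The next paragraph adds an allowance for attrition. On the rate, it says "we anticipate a dropout rate of approximately 20" per cent. It then makes 30 the number to be evaluable and 36 the number to be recruited, and prints the working: "to achieve our target of 30 evaluable patients, we plan to initially recruit 36 patients (30/0.8").

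That paragraph ends with an inference drawn from the allowance: "This approach will help guarantee that our findings are statistically significant and reflective of the broader population" of such patients.

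The abstract gives one number only and attaches it to enrolment: "a prospective pilot study will enroll 30 consecutive patients diagnosed with eTNBC".

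**The concern.** Three statements about the size of the study do not fit together.

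- **The recruitment figure.** The formula and its result stand side by side and disagree. A reader who relies on 36 will expect 30 evaluable patients, and the plan's own dropout rate does not deliver them.
- **The enrolment figure.** If the abstract governs, recruitment stops at 30. If section 2.7.1 governs, it stops at 36. Only the second is consistent with aiming for 30 evaluable.
- **The assurance.** The section credits the attrition margin with helping to secure statistical significance and representativeness. Recruiting extra patients to replace expected dropouts keeps the analysed number near its target. It does not make an effect exist, and it does not make the patients at one hospital resemble the wider population.

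At stake is whether the one section that justifies the study size can be taken at its word. No decision rule or stated power depends on it.

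**Working it through.** **Inputs, all from section 2.7.1 except the last**

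- Target evaluable: 30.
- Anticipated dropout: d ≈ 0.20.
- Planned recruitment: 36, shown as 30/0.8.
- Basis for 30: earlier studies. No significance level, power, effect size or standard deviation is attached to it.
- Abstract: 30 enrolled.

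**Step 1. Reproduce the printed figure.** The number to recruit so that n remain after a proportion d drops out is n/(1 − d):

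30/(1 − 0.20) = 30/0.8 = 37.5, rounded up to 38.

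This is the formula the section prints, and it does not give 36. Multiplying by (1 + d) does:

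30 × 1.20 = 36.

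The result is therefore exactly what a different calculation from the printed one would give. Rounding cannot take 37.5 to 36.

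**Step 2. What 36 recruits deliver.**

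- Expected evaluable at 20% dropout: 36 × 0.8 = 28.8.
- Largest dropout at which 36 recruits still leave 30: 1 − 30/36 = 16.7%.
- Expected evaluable with 38 recruits: 38 × 0.8 = 30.4.
- Shortfall against the target: 30 − 28.8 = 1.2 patients.

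**Step 3. Sensitivity to the approximate rate.** The section says approximately 20%, so the rate is varied here. The 15% and 25% values are assumptions. The last two columns also assume that patients drop out independently of one another (binomial).

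| Dropout | Needed, 30/(1 − d) | Expected evaluable from 36 | Chance of at least 30, from 36 | Chance of at least 30, from 38 |
|---|---|---|---|---|
| 15% | 35.3 | 30.6 | 71% | 89% |
| 20% | 37.5 | 28.8 | 40% | 66% |
| 25% | 40.0 | 27.0 | 17% | 36% |

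At 20%, 36 recruits are more likely than not to fall short of 30. With 38 the expected number reaches 30, but a shortfall still occurs about one time in three. Neither number secures 30.

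**Step 4. How much the shortfall matters.** The plan states no precision or power, so two yardsticks are assumed: a one-sample test of change at two-sided 5% with 80% power, and a 95% Wilson interval at an observed response of 50%.

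| Evaluable | Smallest detectable change | Interval at 50% response |
|---|---|---|
| 30 | 0.529 SD | 33.2% to 66.8% |
| 29 | 0.539 SD | 32.9% to 67.1% |

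Only the difference between the rows bears on this error, and it is negligible. The rows themselves describe any study of about this size.

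**Step 5. Set the enrolment statements side by side.** The abstract enrols 30. Section 2.7.1 recruits 36 so that 30 are evaluable. If only 30 were enrolled, 20% dropout would leave 30 × 0.8 = 24.

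**Step 6. Test the assurance.** The margin changes one quantity, the expected number evaluable. Whether a result is significant depends on the true effect, its variability and the test, and none of these entered the choice of 30. Representativeness depends on who is eligible, who is approached and who stays, and extra recruits from the same source do not change that.

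**The case against.** The strongest reply is that this is a single-centre pilot whose size comes from precedent. No power or precision is stated, so none is lost, and step 4 shows that 29 in place of 30 changes nothing of substance. That stands, and it settles the severity.

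It can also be said that the dropout rate is only approximate, and that at 15% the figure of 36 would be enough. That does not rescue the text, because the section itself divides by 0.8.

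On the enrolment numbers, the opening sentence of section 2.7.1 can be read as describing the 30 evaluable patients named later. That reading is fair. The clear conflict is with the abstract, which speaks of enrolling 30.

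On the assurance, the wording is that the approach will help guarantee significance, which is softer than a promise. A reader might infer that the plan claims assured significance, or that a null result is bound to be misread. The text does not go that far, and nothing in the article ties the interpretation of a null result to this sentence. The softer wording is still unsupported, for the reason in step 6.

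A reader might also set the precedent cited for the sample size against the Discussion's remark that only one completed trial showed a significant effect on pain, and infer that the chosen size has already failed. The documents do not support that. The Discussion does not say whether the study cited as the precedent was completed, how large it was or what it found. A pilot may also take its size from an earlier study whatever that study's result.

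Finally, the absence of power inputs is not a defect here. The article declares a precedent-based size for a pilot.

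**Conclusion.** The point holds as a minor correction. The printed equation is wrong: 30/0.8 is 37.5, so 38, while 36 is 30 × 1.2. At the plan's own 20% dropout, 36 recruits leave about 29 evaluable patients (28.8 expected), and 36 is enough only up to 16.7% dropout. This part is plain arithmetic on the document's figures. Only the probabilities of reaching 30 rest on an assumption, that of independent dropout.

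The abstract's enrolment of 30 conflicts with recruiting 36, and the assurance about significance and representativeness does not follow from an attrition margin.

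A reader might take this as evidence that the study is underpowered or that its conclusions are at risk. The documents do not support that: the gap is about 1.2 expected patients, and there is no stated power to lose.

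**What to change.** 1. **Recruitment figure, section 2.7.1.** Either keep 36 and say that it yields about 29 evaluable patients at 20% dropout (equivalently, that it allows for 16.7%), or replace it with 38 and show 30/0.8 = 37.5, rounded up.
2. **Consistent numbers.** State the recruited number and the evaluable number separately, with the same values in the abstract and in section 2.7.1. Make clear in the opening sentence of 2.7.1 which of the two the 30 refers to.
3. **Assurance.** Delete the claim that the margin helps to guarantee significant and representative findings. Say only that it protects the number of evaluable patients.

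The cost is wording alone if 36 is kept, and two more recruits if 38 is chosen.

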#### 2.7.2. Analysis

Detailed clinical and demographic variables will be recorded for each patient. Frequency tables and descriptive statistics (mean, standard deviation, percentage, median, range) will be used to summarize patient characteristics. 

Both the total score and the score for each domain will be calculated for each questionnaire, according to the nature of the questionnaire. The expected overall clinical improvement will be assessed based on the variation in the total scores of the administered assessment questionnaires at different timepoints (T0, T1, and T2). A positive response to PNE is defined as a 50% or greater improvement in patient-reported outcomes.

Changes in the levels of serum biomarkers between T0 and T2 (baseline and end of training) will be separately analyzed among patients who have responded to PNE (defined as an improvement in patient-reported outcomes of at least 50%) compared to non-responders using a generalized linear model in which the factors involved in the analysis will be the groups (responders/non-responders) and the timepoints (intra-group variable).

As variables of interest and covariates, demographic data, education level, comorbidities, risk factors for BC (e.g., body mass index, cigarette smoking), and menopausal status at diagnosis will be recorded. Additional covariates to be considered include anxiety and depression, which are closely linked to the perception of pain and the experience associated with it.

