### 2.3. Participant Recruitment and Study Procedures

This project will involve the consecutive enrollment of early TNBC patients with the onset or worsening of a PS (NRS ≥4) who meet the inclusion criteria of the study. 

The evaluation of QoL, perceived pain, and disability will be carried out at baseline (T0) and approximately 5 weeks after the start (T1) and at the end (T2) of PNE; finally, an additional assessment will be performed 6 months after the end of PNE. This evaluation will be conducted using validated questionnaires that measure the overall QoL of BC patients (European Organization for Research and Treatment of Cancer Quality of Life Questionnaire, Breast Cancer-Specific 23 [EORTCQLQ-BR23] questionnaire), pain (NRS), migraine and headaches (Headache Impact Test-6 [HIT-6] and MIgraine Disability ASsessment [MIDAS] questionnaires), and anxiety and depression (Hospital Anxiety and Depression Scale [HADS]).

At timepoints T0 and T2, a peripheral venous blood draw will be collected for the execution of a panel of blood chemical tests (CRP, ESR, Interleukin [IL]-6, IL-8, tumor necrosis factor [TNF]-α, and CGRP, as well as NLR calculation).

Our program involves the administration of a 10-session PNE program on a weekly basis (total of 10 weeks of intervention), in addition to the standard of care, according to the level of pain. The PNE sessions will be conducted by a physiotherapist expert in delivering PNE across different chronic pain populations, with more than 10 years of experience. Each session will be delivered in small groups (3–5 people) using a PowerPoint slide presentation and will last approximately one hour. A part of each session will be dedicated to questions and answers and personal discussion about personal experience.

The contents of the 10 sessions will be as follows:The concept of pain and its biological function.Common misconceptions about pain and its origin.The basics of the neurobiology of pain.What factors alter the perception of pain?The concept of the nervous system as a “protomet” and other metaphors.What happens when pain persists and becomes chronic?How can I train my nervous system?The importance of context, emotional aspects, and communication.The importance of stress management.Long-term pain management.

The program was structured starting from the books “*Explain pain*” [29] and “*Explain pain supercharged*” [30,31], written by the leading researchers on the topic of PNE.

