### 2.4. Objectives

Primary objective:The primary objective of the project is to evaluate, through the use of validated questionnaires, whether the implementation of a dedicated PNE and cognitive training program can lead to clinical improvement in terms of QoL and pain in patients with early-stage TNBC.

Secondary objectives:To assess the impact of PNE on headaches/migraine in patients affected by this condition prior to the start of the program.To evaluate the impact of PNE on anxiety/depression symptoms according to the score of the planned scales.To investigate whether serum levels of inflammatory biomarkers correlate with PSs.To investigate whether serum levels of inflammatory biomarkers before and after PNE treatment correlate with the response to PNE.To compare the results at the end of PNE (T2) with those at six months after the end of the program.

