### 2.5. QoL Evaluation

The assessment of QoL, perceived pain, and disability in TNBC patients will be carried out at baseline and during and after training (T0, T1, and T2, respectively) using the following questionnaires (Table 1):EORTCQLQ-BR23: This questionnaire is derived from the integration of the general questionnaire for cancer patients (EORTC QLQ-C30) with topics specifically relevant to BC. It consists of 23 items grouped into 5 domains that evaluate the side effects of therapy, disorders at the level of the arm subjected to axillary lymph node surgery, disorders at the breast level, the perception of one’s body image, and sexual functioning. The scores are linearly converted into a scale from 0 to 100. For the functional scales (body image, sexuality, and future expectations), higher scores reflect a better condition, while for symptom scales, higher scores represent worse symptom levels [32,33].NRS: This one-dimensional intensity scale assesses the symptom of pain in a simple, immediate, and easily reproducible way (score from 0 to 10) [34].HIT-6: This test measures the impact of migraines on common daily activities. It was also validated in the Italian population. It consists of 6 questions concerning how often headaches have caused severe pain, how often they have interrupted daily activities, how often they have resulted in the complete interruption of activities with the need to rest, the presence of headache-related fatigue, irritability, and difficulty concentrating [35]. The possible values for each question are expressed through a Likert scale from 1 to 5 (never, rarely, sometimes, very often, and always) with which a numerical score value is associated (6, 8, 10, 11, 13), and therefore, the total score can range from 36 to 78.MIDAS: This questionnaire is widely used to measure the impact of headaches on the individual’s ability to be efficient at work, school, and social activities over the previous 3 months in terms of days of activity lost due to the headache [36]. It consists of 7 items, the first 5 of which evaluate the complete loss of or at least a 50% reduction in productivity (whether work, school, or household). The number of days lost is counted to give the final score. The frequency and intensity of headaches are explored in the last 2 questions. Based on the scores, a disability threshold from 1 to 4 is defined, where the fourth level, the most serious, starts from a score of 21.HADS: This scale is used to evaluate the presence and intensity of anxiety and depression symptoms in enrolled patients. This is the most widely used questionnaire for screening for anxiety and depression, validated both in the general population and in patients with a wide range of medical conditions, including patients with BC [37,38]. The scale consists of 14 items divided into two subscales (anxiety and depression) with 7 items each. Each item is assigned a score from 0 to 3, and the total score of each scale is 21 points, where a higher score refers to greater symptomatology. Specifically, a score from 11 to 21 indicates clinically significant cases of anxiety or depression.

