
**Table 1 jpm-14-00711-t001:** Questionnaires that will be used for the assessment of QoL, perceived pain, and disability in TNBC patients at baseline and during and after training.

Domain	Questionnaire	Description	Scaling	Ref.
QoL	EORTCQLQ-BR23	23 items on side effects, disorders at the axilla and the breast(s), body image, and sexual functioning	From 0 to 100	[32,33]
Pain	NRS	one-dimensional intensity scale	From 0 to 10	[34]
Psychological	HADS	14 items on anxiety and depression	From 0 to 21 (for each 7-point scale)	[37,38]
Headache	HIT-6	6 questions on the impact of migraine on common daily activities	From 36 to 78	[35]
Headache	MIDAS	7 items on the impact of headaches on individual efficiency at work, school, and social activities	From to 28	[36]

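### Clinical improvement is judged on questionnaire total scores, but BR23, the only QoL instrument, is described as separate scales running in opposite directions, with no rule for a total

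*Protocol article*

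**What the plan says.** The primary objective (Section 2.4) asks whether the programme "can lead to clinical improvement in terms of QoL and pain in patients with early-stage TNBC". Section 2.3 introduces BR23 among "validated questionnaires that measure the overall QoL of BC patients", and Table 1 assigns the QoL domain to BR23 alone. The general QLQ-C30 appears only in Section 2.5, as the questionnaire from which BR23 was derived. It is not in the list of instruments to be given in Section 2.3, Section 2.5 or Table 1.

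Section 2.5 describes the content of BR23: "It consists of 23 items grouped into 5 domains that evaluate the side effects of therapy", followed by arm problems, breast problems, body image and sexual functioning. On scoring it says: "The scores are linearly converted into a scale from 0 to 100". On direction, for the functional scales "higher scores reflect a better condition, while for symptom scales, higher scores represent worse symptom levels". Table 1 summarises the instrument as "23 items on side effects, disorders at the axilla and the breast(s), body image, and sexual functioning" and gives one range, 0 to 100, with no direction.

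Section 2.7.2 then sets the analysis in two steps. First: "Both the total score and the score for each domain will be calculated for each questionnaire, according to the nature of the questionnaire". Second: "The expected overall clinical improvement will be assessed based on the variation in the total scores of the administered assessment questionnaires", over T0, T1 and T2. The same section defines a responder by an improvement of at least 50% in patient-reported outcomes, and uses that split for the biomarker comparison.

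**The concern.** A total score suits an instrument whose items all point the same way. By the article's own description, BR23 is not such an instrument. The analysis sentence nevertheless makes change in totals the measure of improvement, without exempting BR23 or saying how its total would be built.

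What is at stake is the QoL half of the primary objective. A total of unaligned scales has no fixed meaning for up or down, so a change in it cannot be read as benefit or harm. The responder rule is exposed to the same problem, because a percentage improvement needs a known direction, and the responder split feeds the biomarker analysis. A second, smaller issue is the label: the article says the instrument captures overall QoL, while the domains it lists are specific ones.

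**Working it through.** The plan gives no figure for a BR23 total, so there is nothing to reproduce. The check asks what each reading of Section 2.7.2 would deliver.

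**Inputs from the article (Section 2.5)**
- Five listed domains: therapy side effects, arm, breast, body image, sexual functioning.
- Each scale runs from 0 to 100.
- Body image and sexuality are named as functional (higher is better). The other three listed domains are treated here as symptom scales (higher is worse).

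**Assumptions made for illustration**
- Baseline of 50 on every scale.
- The sizes of change shown below.
- The total is the mean of the five scales. A sum is five times the mean and leads to the same conclusion.

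**Formulas** (S = symptom score, F = functional score)
- Unaligned mean = (S1 + S2 + S3 + F1 + F2) / 5
- Aligned mean = [(100 − S1) + (100 − S2) + (100 − S3) + F1 + F2] / 5

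Both equal 50 at baseline. Every patient below improves on all five scales.

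| Patient | Symptom scales | Functional scales | Unaligned mean after | Change | Aligned mean after | Change |
|---|---|---|---|---|---|---|
| A | 50 to 40 | 50 to 60 | (3×40 + 2×60)/5 = 48 | −2 | (3×60 + 2×60)/5 = 60 | +10 |
| B | 50 to 40 | 50 to 65 | (3×40 + 2×65)/5 = 50 | 0 | (3×60 + 2×65)/5 = 62 | +12 |
| C | 50 to 30 | 50 to 60 | (3×30 + 2×60)/5 = 42 | −8 | (3×70 + 2×60)/5 = 66 | +16 |

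Section 2.5 also mentions future expectations as a functional scale, although it is not among the five domains listed. Counting it gives three scales in each direction. An equal 10-point improvement on all six then gives (3×(−10) + 3×10)/6 = 0 unaligned, and +10 aligned.

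**Effect on the responder rule.** For patient C the unaligned total changes by −8/50 = −16%, and the aligned total by +16/50 = +32%. The same patient moves in opposite directions according to a choice that the article does not state.

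**The three readings of Section 2.7.2**
1. Scales combined as scored: improvements cancel or change sign, as in the table.
2. Symptom scales reversed first: the direction is sound, but the endpoint is a composite that the article neither defines nor describes as validated, although Section 2.4 relies on validated questionnaires.
3. The qualifier about the nature of each questionnaire means that BR23 has no total: the sentence tying improvement to totals then provides no analysis variable for QoL.

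**The case against.** The strongest reply is that the article never says the BR23 scales are added unreversed. The sentence on scoring carries a qualifier about the nature of each questionnaire, Section 2.5 shows that the authors know the scales run in opposite directions, and a scoring algorithm is a detail that a journal article may leave to the full protocol or SAP. Domain scores are also to be calculated, so scale-level BR23 results will exist.

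Much of this stands. A reader might infer that the plan sums opposed scales, so that a patient who improves everywhere will show no change. The documents do not support that as a fact: reversal is neither stated nor excluded. Nor is zero the general result. Equal 10-point gains on the five listed domains give −2, and zero needs particular values such as those of patient B. A reader might also infer that the trial could say nothing about QoL, which goes too far given the planned domain scores. The statement that BR23 has no global scale likewise rests only on a condensed and visibly incomplete list, and supports no more than that none is listed.

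What the reply does not remove is the positive statement that improvement is judged on totals. The article does not merely omit a scoring detail. It names a measure that its own description of BR23 does not supply, and the planned domain scores are given no role in judging improvement.

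**Conclusion.** Wrong as written, of moderate severity. The total-score rule does not fit the only QoL instrument, so the QoL half of the primary objective has no clearly defined measure under any of the three readings.

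The size is conditional. If the scales are combined as scored, patients who improve on every scale can show changes of −2, 0 or −8 where an aligned mean would show +10, +12 or +16. Those figures rest on the assumed baseline of 50, the assumed changes and equal weighting of the five listed domains. They illustrate the mechanism and do not predict the trial's result.

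The severity is held at moderate for three reasons: this is a pilot of 30 patients, the pain half of the objective uses the NRS, which is a single 0 to 10 scale untouched by this point, and the scale scores needed for the repair are already planned.

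**What to change.** In Section 2.7.2, exempt BR23 from the total-score rule. State that:
- no BR23 total will be used;
- the QoL assessment rests on the BR23 scale scores already planned, each analysed in its own direction;
- one named scale, fixed before any data are examined, carries the QoL objective, the choice being the sponsor's;
- where the 50% responder rule is applied to QoL, it refers to that scale and its stated direction of improvement.

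In Sections 2.3 and 2.4, limit the QoL conclusion to the chosen domain and drop the claim to overall QoL.

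The cost is a change of wording, with no new data collection. The downside is a narrower QoL claim. A sponsor who wants to keep a claim about overall QoL could instead add a questionnaire with a global scale at the same visits. That is an optional design addition with some extra burden for patients, and the correction does not depend on it.

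### The 50% responder rule names no deciding instrument or formula, and on raw scores it cannot be met from HIT-6 baselines below 72 or BR23 functional baselines above 66.7

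*Protocol article*

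**What the plan says.** Section 2.7.2 (Analysis) first says that overall improvement will be judged "based on the variation in the total scores of the administered assessment questionnaires at different timepoints (T0, T1, and T2"). The next sentence sets the responder rule: "A positive response to PNE is defined as a 50% or greater improvement in patient-reported outcomes". The following paragraph repeats the threshold when it forms the two groups for the biomarker model, with responders "defined as an improvement in patient-reported outcomes of at least 50" per cent.

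Section 2.5 (QoL Evaluation) describes the scales the rule would act on:

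- **HIT-6:** six questions, for each of which "a numerical score value is associated (6, 8, 10, 11, 13"), so that "the total score can range from 36 to 78".
- **BR23:** "The scores are linearly converted into a scale from 0 to 100". On the functional scales "higher scores reflect a better condition, while for symptom scales, higher scores represent worse symptom levels".
- **NRS:** 0 to 10. Sections 2.2 and 2.3 require at least 4 at entry.
- **HADS:** 0 to 21 per subscale.
- **MIDAS:** a count of days lost to headache.

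Section 2.4 gives QoL and pain as the primary objective. Headache is a secondary objective, for patients who had it before the programme. Sections 2.3 and 2.6 place the blood draws at T0 and T2. Section 2.7.1 says that enlarging the cohort to 50, to look for factors linked to response, will be considered after preliminary analyses.

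**The concern.** A percentage improvement is comparable across instruments only if each has a true zero at the good end and room to move. That holds for the NRS in this population. It does not hold for HIT-6, whose best possible score is 36, or for the BR23 functional scales, where improvement means moving up towards a cap of 100. A BR23 total has a further problem: its functional and symptom scales run in opposite directions, so percentage improvement in a combined score has no clear meaning without recoding, and the article describes none.

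The responder label forms the grouping factor in the biomarker model and would naturally be the outcome in any search for predictors. With about 30 patients, five instruments and no named decider, the same data can yield quite different responder groups. If the choice is made after the data are seen, the biomarker comparison becomes data-driven.

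**Working it through.** **Inputs.** Item scores, ranges and directions are from section 2.5, the entry NRS from section 2.2, and the 50% threshold from section 2.7.2. The check assumes percentage change from baseline in the raw score; the article states no formula.

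**1. HIT-6 range reproduced.** 6 × 6 = 36 and 6 × 13 = 78, as stated.

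**2. HIT-6 reachability.** Lower is better and the floor is 36. From baseline b the largest improvement is (b − 36)/b, so 50% needs b/2 ≥ 36, that is b ≥ 72.

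| Baseline | Largest possible improvement |
|---|---|
| 50 | 14/50 = 28.0% |
| 60 | 24/60 = 40.0% |
| 70 | 34/70 = 48.6% |
| 72 | 36/72 = 50.0% |
| 78 | 42/78 = 53.8% |

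From 72 the patient must finish at 36, the lowest answer on all six items. From 78 she must finish at 39 or less.

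Of the 5^6 = 15,625 answer patterns, 99 total 72 or more: 99/15,625 = 0.6%. These fall on 6 of the 40 attainable totals (72, 73, 74, 75, 76 and 78). This counts answer patterns, not patients; the article gives no HIT-6 distribution.

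**3. BR23 functional scales.** Higher is better and the ceiling is 100. A 50% gain needs 1.5b ≤ 100, that is b ≤ 66.7.

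- From 75 the most possible is 25/75 = +33.3%.
- From 83.3 the most possible is 16.7/83.3 = +20%.
- From 20 a gain of 10 points is enough (10/20 = 50%), and from 30 a gain of 15 points (15/30 = 50%).
- At a baseline of 0 the percentage is undefined.

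**4. BR23 symptom scales, HADS and MIDAS.** The floor is 0, so 50% is reachable from any non-zero baseline and undefined at 0.

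**5. NRS.** Eligible baselines are 4 to 10. In whole points the targets are 4→2, 5→2, 6→3, 7→3, 8→4, 9→4 and 10→5. All can be reached.

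**6. How much the combination rule could matter (illustration only).** Suppose each of five instruments independently had chance p of showing a 50% improvement without any effect of PNE. Then *any of five* labels 1 − (1 − p)^5 as responders and *all five* labels p^5.

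| p (assumed) | Any of five | All five |
|---|---|---|
| 5% | 1 − 0.95^5 = 23% | below 0.01% |
| 15% | 1 − 0.85^5 = 56% | below 0.01% |
| 30% | 1 − 0.70^5 = 83% | 0.24% |

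The article supplies no value for p, and independence is doubtful because section 2.7.2 itself links anxiety and depression to pain. Setting HIT-6 to zero chance at p = 15% gives 1 − 0.85^4 = 48%. Only the wide gap between the two readings should be taken from this table.

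**The case against.** The strongest reply has four parts.

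- **The formula is not stated.** A percentage measured above the floor removes the HIT-6 barrier: a baseline of 60 would need 48 or less, and 78 would need 57 or less. This stands, which is why the arithmetic is tied to raw scores. But the article gives no such formula, and rescaling HIT-6 would settle neither the BR23 ceiling nor the choice of instrument.
- **HIT-6 is peripheral.** It serves a secondary objective in patients who already have headache, so requiring all five instruments to improve in every patient is an unlikely reading. This also stands. The BR23 limit, however, falls on the QoL half of the primary objective.
- **The detail may sit in an analysis plan.** The deciding instrument, the handling of zeros and the timepoint are often fixed there, and the T0 to T2 biomarker comparison already points to T2. Missing detail alone would be no finding. Here the article states the threshold twice, alongside an assessment on total scores, and applied to those scores it fails over large parts of two scales.
- **The label does not carry the whole primary objective.** Section 2.7.2 also assesses improvement by score variation over time, and the label's only explicit use is the biomarker comparison. The enlargement to 50 is conditional. All of this is correct and limits the consequence.

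A reader might infer that HIT-6 can never meet the rule, that responder status says nothing about PNE, or that the rule alone decides success on the primary objective. The documents support none of these. HIT-6 baselines of 72 to 78 can meet it, the NRS can meet it in every eligible patient, and the primary objective is also assessed by change in scores.

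**Conclusion.** The point holds in limited form. One percentage rule is applied to scales on which it means different things, with no deciding instrument or formula. On raw scores it is unattainable for HIT-6 baselines below 72 and BR23 functional baselines above 66.7, and undefined at a baseline of 0; on the NRS it works for all eligible patients. A patient who improves as far as her scale allows can therefore be classed a non-responder on HIT-6 or a BR23 functional scale.

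Responder status thus depends partly on the instrument chosen, and this carries into the biomarker model and any later predictor analysis. The two thresholds follow exactly from the stated ranges, given raw percentage change. How many patients would be misclassified cannot be computed, because the article gives no baseline distributions.

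**What to change.** Before any outcome data are examined, amend section 2.7.2 as follows.

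1. For the biomarker analysis, define a responder as a patient with at least a 50% reduction in NRS from T0 to T2. This is one outcome over one interval, it is reachable from every eligible baseline, and it matches the two blood draws.
2. Do not apply the raw 50% rule to HIT-6, BR23, HADS or MIDAS. Report the mean absolute change from T0 with a 95% CI for each, with BR23 given scale by scale in its own direction.
3. If a percentage is wanted for HIT-6, compute it on (score − 36).
4. If predictors of response are later sought, use the same label.

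**Cost:** one paragraph of analysis wording and no new data. The real trade-off is that QoL, the other half of the primary objective, becomes a separately reported continuous outcome and no longer forms part of the responder label.
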